## Abstract

**Background::**

Patients who undergo gastrectomy for gastric cancer experience gastrointestinal symptoms, psychological responses, and social problems. These factors reduce a patient’s quality of life (QoL) after surgery. A web-based platform (Wecare^®^) has been developed to address distress and provide solutions. This study aimed to evaluate whether Wecare® improved the QoL of patients who underwent gastrectomy.

**Methods::**

A total of 88 patients who undergo gastrectomy for gastric cancer will be randomly allocated to either the “Wecare^®^” group or the control group at a 1:1 ratio. After using the “Wecare^®^” platform for the first 22 patients and making modifications, the next 66 patients will be randomized equally. The primary outcome of this trial is the QoL among gastric cancer survivors (KOQUSS-40). The values of weight change, nutritional index change, KOQUSS-40 questionnaire compliance, self-efficacy, physical activity change, and satisfaction will be compared between the two groups as secondary outcomes. The investigator will follow-up with the patients at 1, 3, and 6 months after surgery at the outpatient clinic.

**Discussion::**

This is the first randomized controlled trial to analyze the usefulness of a symptom management platform (Wecare^®^) among gastric cancer survivors. This study aimed to verify the efficacy of web-based platforms in relieving discomfort after gastric cancer surgery. Future large-scale clinical trials are planned.

Highlights
First randomized controlled trial evaluating a digital symptom management platform (Wecare®) for gastric cancer survivors after gastrectomy.Wecare® provides personalized, algorithm-driven education and expert feedback based on the KOQUSS-40 questionnaire.The platform enables continuous symptom monitoring and enhances postoperative quality of life.This study supports the feasibility of integrating digital health tools into survivorship care after cancer surgery.Findings may lay the groundwork for scalable, patient-centered digital platforms in oncology.

## Introduction

### Background and rationale {6a}

Surgery remains the mainstay of gastric cancer treatment. With the increasing prevalence of early gastric cancer and improved survival rates, especially in East Asia due to nationwide screening programs, the number of long-term survivors has grown steadily^[1–3]^. Consequently, there is a rising focus on improving quality of life (QoL) after gastrectomy. Patients often experience a range of physical symptoms known as post-gastrectomy syndrome, along with psychological distress and social challenges that significantly affect their daily lives^[4,5]^. To address these unmet needs, digital health solutions have gained attention^[6–10]^. Previous randomized clinical trials have examined the effect of smartphone-based interventions in patients with cancer, and the results have revealed that these interventions enhance recovery quality and provide comparable satisfaction with care to conventional in-person follow-ups^[11–15]^.

We care® is a novel, web-based platform specifically designed to support gastric cancer survivors after gastrectomy. Developed by the KOQUSS group, it integrates an intelligent screening system based on the validated KOQUSS-40 questionnaire to identify patient-specific symptoms and needs. Based on this assessment, the platform provides personalized educational content and expert-driven recommendations tailored to the patient’s recovery phase. Furthermore, the results are shared with physicians to facilitate more informed and efficient consultations during outpatient visits.

To the best of our knowledge, this is the first randomized controlled trial to evaluate the impact of a digital symptom management platform on QoL after gastric cancer surgery. This study aims to assess whether Wecare® can enhance postoperative recovery and support long-term survivorship in a cost-effective, scalable way.

### Objectives {7}

The Korean Quality of Life in Stomach Cancer Patients Study Group (KOQUSS) in the Korean Gastric Cancer Association developed a survey tool (KOQUSS-40, Table 1) to appropriately assess the QoL of gastric cancer patients who have undergone gastrectomy and developed a digital platform (Wecare^®^) based on the KOQUSS-40^[16]^. The Wecare^®^ platform conducts assessments by screening for patient needs and symptoms based on questionnaires. It provides patients with reporting and relevant information (including content and videos). The assessment results were also shared with physicians for use as patient information during outpatient clinic visits. **In this study, we propose a randomized controlled trial to compare QoL after gastrectomy in patients with and without Wecare^®^ support.**

**Table 1 T1:** KOQUSS questionnaire*

Over the past week	Very satisfied	Slightly satisfied	Slightly dissatisfied	Very dissatisfied	
1. How is your overall health?	□	□	□	□
2. How is your overall quality of life?	□	□	□	□
3. Are you satisfied with your cancer treatment?	□	□	□	□
4. Are you satisfied with the surgical scars?	□	□	□	□
5. Are you satisfied with the cost of your cancer treatment?	□	□	□	□

Over the past week	Not at all	Somewhat	Quite	Very much
6. Do you feel uncomfortable because you eat slowly in social situation?	□	□	□	□
7. Do you feel uncomfortable because you eat too often?	□	□	□	□
8. Do you feel uncomfortable carrying on with daily life due to lack of energy?	□	□	□	□
9. Has the amount of food intake decreased compared to before surgery?	□	□	□	□
10. Has your appetite reduced?	□	□	□	□
11. Do you feel full even if you ate small amount of food?	□	□	□	□
12. Do you feel food gets stuck in the throat when eating?	□	□	□	□
13. Do you feel something is stuck in the throat when drinking water?	□	□	□	□
14. Do you feel discomfort with fullness in your upper abdomen after eating?	□	□	□	□
15. Do you feel food is regurgitating back up (coming up)?	□	□	□	□

Over the past week	Not at all	Somewhat	Quite	Very much
16. Do you get bitter water from the stomach to your mouth?	□	□	□	□
17. Do you have any burning sensation in your chest?	□	□	□	□
18. Have you ever had abdominal pain with bloating after a meal?	□	□	□	□
19. Have you ever had a heart palpitation after a meal?	□	□	□	□
20. Have you ever had a blush or hot face after a meal?	□	□	□	□
21. Have you ever turned pale after a meal?	□	□	□	□
22. Have you ever had a sudden cold sweat before?	□	□	□	□
23. Have you ever had diarrhea after a meal?	□	□	□	□
24. Have you ever had any abdominal pain that is not related to eating?	□	□	□	□
25. Do you feel uncomfortable due to gas pains?	□	□	□	□
26. Do you feel uncomfortable due to frequent bowel movement?	□	□	□	□
27. Do you feel uncomfortable due to frequent wind?	□	□	□	□
28. Do you feel uncomfortable with constipation?	□	□	□	□
29. Do you have hard stool?	□	□	□	□
30. Have you ever been nervous?	□	□	□	□
31. Have you ever been depressed?	□	□	□	□
32. Have you ever felt lethargic?	□	□	□	□
33. Do you have insomnia?	□	□	□	□
34. Have you ever suddenly been dizzy and wanted to sit down?	□	□	□	□
35. Are you worried about losing weight?	□	□	□	□
36. Are you reluctant to go to the bathroom or pool because of a surgical scar?	□	□	□	□
37. Are you worried about your stomach cancer coming back?	□	□	□	□
38. Do you have pain in your surgical scar?	□	□	□	□
39. Do you have itchiness in your surgical scar?	□	□	□	□
40. Do you have financial difficulty because of the cost of your cancer treatment?	□	□	□	□

* Questions below ask you about your post-surgery health, quality of life, and satisfaction. Please check (v) to indicate the extent to which you are satisfied in regard to how you have been past week.

### Trial design {8}

This randomized controlled multicenter trial with two parallel groups aims to evaluate the efficacy and safety of a web-based intervention program, named “Wecare^®^.” The primary endpoint will be QoL among survivors of gastric cancer. The investigator will examine the patients 1, 3, and 6 months after surgery (Fig. 1).

**Figure 1. F1:**
[figure not shown]
Flow diagram of the Wecare^®^ study.

## Methods: participants, interventions, and outcomes

### Study setting {9}

This study enrolled participants who underwent radical gastrectomy at 11 participating teaching hospitals in the Republic of Korea, one of the countries with the highest incidence of gastric cancer. This study was approved by the Institutional Review Board of the Hospital.

### Eligibility criteria {10}

Patients with gastric cancer aged 19–75 years who are indicated for gastrectomy will be eligible for this study. To be included, the patient should be operable and gastric cancer should be surgically removable (stages I–III). Patients who could not be followed up regularly, were illiterate, or did not consent to participate in the study were excluded. In addition, patients with severe psychiatric disorders, significant comorbidities, inability to communicate effectively, or other medical or personal conditions deemed inappropriate for participation by their attending surgeon were also excluded. Informed consent was obtained from all participants.

### Who will obtain patient informed consent? {26a}

Investigators will thoroughly explain the trial details to the potential participants and provide patient informed consent. Participants were given sufficient time to consider their decision to join the trial. They could then sign the informed consent form and were free to withdraw at any time during the trial. Written informed consent was obtained from the patient for publication. A copy of the written consent is available for review by the Editor-in-Chief of this journal on request.

### Additional consent provisions for the collection and use of participant data and biological specimens {26b}

No additional biological samples were collected for this study. However, standard clinical laboratory data, including hemoglobin, albumin, and lymphocyte counts, were obtained as part of routine postoperative care and used for evaluating nutritional status.

## Interventions

### Explanation for the choice of comparators {6b}

In the intervention group, the participants were asked to use the Wecare^®^ platform (Fig. 2A~I). The Wecare^®^ platform administers QoL questionnaires, including the KOQUSS-40, following gastrectomy for gastric cancer. Based on participants’ responses, the platform automatically generates expert recommendations from gastric cancer specialists based on participants’ responses according to the timing of surgery after gastrectomy (Fig. 2C~E). Furthermore, the Wecare^®^ platform offers educational materials for gastric cancer to address the participants’ questions about the disease (Fig. 2F~I). Participants will be free to use the platform but will be asked to visit the Wecare^®^ platform at least once a month and answer questionnaires. The participants will visit an outpatient clinic before surgery and at 1, 3, and 6 months after surgery.

**Figure 2. F2:**
[figure not shown]
Screenshots from Wecare^®^ application used by patients. **A** shows the patient’s basic information. **B** displays the diet and NRS2002 results. **C** evaluates the scores for each domain of the KOQUSS-40 questionnaire, where white indicates no to mild symptoms, blue represents intermediate symptoms, and red shows severe symptoms. **D** compares the patient’s values in each domain with the average values of a small group matched for age, gender, and operation period within an existing patient group. **E** provides automated responses regarding education and treatment for domains showing severe symptoms. **F** contains recommended educational materials from medical professionals about symptoms based on the patient’s postoperative timeline. **G** features educational materials in a card news format, primarily composed of images. **H** provides educational materials centered on text. **I** consists of educational materials presented in video format.

In the control group, participants will be asked to complete written questionnaires in the outpatient clinic before surgery and 1, 3, and 6 months after surgery. Based on the questionnaires, the clinician provides a solution at an outpatient clinic. However, the Wecare^®^ platform is not available.

### Intervention description {11a}

To understand the feasibility of participant recruitment or study design at all participating sites, we planned to determine the number of participants in two phases. In the first phase, 22 patients will be recruited from 11 institutions (two patients per institution) to collect patient data using the draft protocol and correct any problems, and 66 patients will be recruited from 11 institutions (6 patients per institution) to measure outcome variables preoperatively and at 1, 3, and 6 months postoperatively, according to the revised protocol. The number of subjects required for the main study was calculated based on the data from the second phase. Each participating hospital is expected to enroll a sufficient number of eligible patients because the incidence of gastric cancer in South Korea is very high and participating institutions perform a large number of gastric cancer surgeries each year.

The Wecare® platform aims to improve postoperative quality of life through multiple integrated mechanisms. Patient-reported outcomes are collected via the KOQUSS-40 questionnaire at regular intervals, enabling continuous monitoring of physical, psychological, and social symptoms. Based on these responses, the platform delivers algorithm-based personalized content, including tailored educational resources (text, image, and video formats) and automated feedback aligned with each patient’s symptom profile and recovery phase. The platform stratifies symptoms by severity and provides immediate guidance or recommendations for self-management. These results are also shared with physicians before outpatient visits, facilitating more informed clinical decision-making. This integrated, patient-centered digital approach is expected to promote self-efficacy, reduce symptom burden, and ultimately enhance overall QoL following gastrectomy.

### Criteria for discontinuing or modifying allocated interventions {11b}

There were no predetermined criteria for discontinuing or modifying the interventions assigned to participants. All individuals participated voluntarily and had the option to discontinue the study at any time for any reason without negative consequences.

### Strategies to improve adherence to interventions {11c}

This clinical trial will recruit patients with cancer who will require regular follow-up to assess cancer recurrence. We anticipate that this will improve the adherence to the study protocol.

### Relevant concomitant care permitted or prohibited during the trial {11d}

This clinical trial is not related to the surgery or drug itself but rather to the quality of daily life after surgery. Therefore, no relevant concomitant postoperative care or intervention was permitted or prohibited during the trial.

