### Outcomes {12}

The primary outcome of this trial was the QoL of the gastric cancer survivors (KOQUSS-40). The KOQUSS-40 questionnaire was developed and validated to evaluate the QoL of patients with gastric cancer who underwent gastrectomy. The questionnaire included 40 items across 11 domains, focusing on QoL related to postgastrectomy symptoms^[16]^. Using this questionnaire, we will compare each item and domain score between the groups before surgery and at 1, 3, and 6 months after surgery in the outpatient clinic.

Weight, nutritional parameters, questionnaire compliance, self-efficacy, and physical activity were compared between groups as secondary outcomes. Nutritional parameters, such as hemoglobin, albumin, and lymphocytes, and the prognostic nutritional index will be measured using common laboratory tests. Information on satisfaction with the Wecare^®^ program will also be collected.

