## Assignment of interventions: allocation

### Sequence generation {16a}

Eligible patients will be randomly assigned to either the control or experimental group in a 1:1 ratio. Medical statisticians will perform stratified randomization. This randomization will be performed based on an independent computer-based sequence generated from the implementation of the dynamic algorithm as the stratifying variable.

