## Data collection and management

### Plans for assessment and collection of outcomes {18a}

The baseline demographic, surgical, and pathological characteristics of the patients and outcome variables were collected. Demographic and clinical characteristics were collected using an electronic case report form based on the participants’ electronic medical records. In the intervention group, questionnaire-based data will be collected using tablets at every planned visit, where the electronic questionnaire will be designed to warn the respondent about any missing values or outliers. A written questionnaire was administered to the control group. Because the data will be stored in the data center of the KOCAS ecosystem, central edit checking will be performed for all input data. A manual review of patient data will be performed in case of any error from the edit check.

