### Methods for additional analyses (e.g., Subgroup analyses) {20b}

Subgroup analyses will be performed according to the type of gastrectomy. Additionally, to explore differential effects among patient subsets in terms of age, baseline health status, and comorbidities, we will conduct subgroup analyses.

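### The reason given for setting concomitant care aside does not follow; record postoperative cancer treatment and adjust for pathological stage

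*Protocol article*

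**What the plan says.** Section {11d} of the protocol article gives a premise, "This clinical trial is not related to the surgery or drug itself but rather to the quality of daily life after surgery", and draws a conclusion from it: "Therefore, no relevant concomitant postoperative care or intervention was permitted or prohibited during the trial".

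Other sections bear on this:

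- **Eligibility {10}:** "gastric cancer should be surgically removable (stages I–III").
- **Outcomes {12}:** for KOQUSS-40, "we will compare each item and domain score between the groups before surgery and at 1, 3, and 6 months after surgery". For the secondary outcomes, weight is compared and "Nutritional parameters, such as hemoglobin, albumin, and lymphocytes, and the prognostic nutritional index will be measured using common laboratory tests".
- **Assessment and collection {18a}:** "The baseline demographic, surgical, and pathological characteristics of the patients and outcome variables were collected". Stage is not named, but it should fall under the pathology data.
- **Sequence generation {16a}:** randomisation is stratified, but the factor is described only as an "independent computer-based sequence generated from the implementation of the dynamic algorithm as the stratifying variable". No patient variable is identified.
- **Statistical methods {20a}:** the primary analysis is a linear mixed model for four measurements per patient. No covariate is listed.
- **Additional analyses {20b}:** "Subgroup analyses will be performed according to the type of gastrectomy". Age, baseline health status and comorbidities are added as further subgroups.

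The article nowhere mentions chemotherapy or other adjuvant treatment, and nowhere says that postoperative treatment will be recorded.

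**The concern.** The premise concerns what the trial studies. The conclusion needs a premise about what can affect the endpoints, and the endpoints here are exposed. KOQUSS-40 asks about energy (item 8), appetite (10), diarrhoea (23) and lethargy (32). Three items refer to cancer treatment itself: satisfaction with it (3), satisfaction with its cost (5) and financial difficulty from that cost (40). The secondary outcomes include weight, haemoglobin, albumin, lymphocytes and the prognostic nutritional index. With stages I–III eligible, some patients may have further cancer treatment between 1 and 6 months while others have none.

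Three things are at stake:

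- **Precision.** Variation that stage could explain stays in the residual. Section {11a} says the main study is sized from second-phase data, so that variation can carry into the next sample size.
- **Chance imbalance.** With 33 to 44 patients per arm, the arms can differ noticeably in stage.
- **Interpretation.** The trial is open label. Platform results reach physicians before visits, and platform users found to need immediate treatment are asked to attend hospital. Care after randomisation may therefore differ by arm. That may be part of the platform's effect, but it cannot be described if it is not recorded.

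**Working it through.** **The plan's own figures.** No power-based figure exists to reproduce, because section {14} states that no formal calculation was done. The counts agree: 11 × 2 = 22, 11 × 6 = 66, and 22 + 66 = 88. At 1:1 this is 44 per arm, or 33 per arm if only the second phase is analysed.

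**Assumptions (not in the article).** The share in stage II–III is p = 0.25 to 0.45. Every stage II–III patient is treated. Treatment worsens an outcome by d = 0.5 to 1 within-group SD. Allocation is not balanced on stage.

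**Step 1: chance of an imbalance of at least 15 points.** This is the exact distribution of the difference between two independent Binomial(n, p) proportions.

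| n per arm | p = 0.25 | p = 0.35 | p = 0.45 |
|---|---|---|---|
| 33 | 0.200 | 0.245 | 0.265 |
| 44 | 0.109 | 0.146 | 0.163 |

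**Step 2: shift in the comparison at that imbalance.** Shift = 0.15 × d, so 0.15 × 0.5 = 0.075 SD and 0.15 × 1 = 0.15 SD. The standard error of a two-group difference is √(2/n): √(2/33) = 0.246 SD and √(2/44) = 0.213 SD. With 33 per arm the shift is 0.075/0.246 = 0.30 to 0.15/0.246 = 0.61 of one standard error.

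**Step 3: outcome variance explained by stage.** R² = 1 − 1/(1 + d²p(1−p)).

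- d = 0.5: 0.045 (p = 0.25) to 0.058 (p = 0.45).
- d = 1: 0.158 to 0.198.

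**Step 4: power, under a separate set of assumptions.** Take 20–40% treated, an effect e of 0.3–0.8 SD, a true difference of 0.5 SD and a two-sided 0.05 level (normal approximation). The unadjusted variance is inflated by 1 + p(1−p)e², where p is now the share treated.

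| n per arm | Factor adjusted for | Not adjusted for | Loss |
|---|---|---|---|
| 33 | 0.528 | 0.523 to 0.472 | 0.5 to 5.6 points |
| 44 | 0.650 | 0.644 to 0.588 | 0.6 to 6.2 points |

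**Step 5: relax the assumption that all stage II–III patients are treated.** If, for illustration, 60% are treated, the shift from a 15-point stage imbalance becomes 0.6 × 0.075 = 0.045 SD to 0.6 × 0.15 = 0.09 SD. The variance explained by stage is then (0.6d)²p(1−p) / (1 + d²q(1−q)) with q = 0.6p, about 2% to 7%.

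Steps 2 and 3 are therefore upper-end values. They also describe a postoperative comparison. The preoperative measurement, one of the four in the mixed model, cannot reflect postoperative treatment.

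**The case against.** The strongest reply is that nothing here is an error. Leaving usual care unrestricted in both arms is a legitimate choice for a trial of a support platform. A journal article may leave its covariate list and case report form to the full protocol or analysis plan. The premise about cancer treatment comes from outside the article. The study also calls itself a pilot for feasibility and preliminary efficacy.

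Much of this stands. Unrestricted care is not the fault, and a model sentence that lists no covariates does not show that there are none. The treatment share and effect are assumptions. What remains is a stated rationale that does not support its conclusion, together with an inexpensive improvement.

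A reader might go further in three ways that the article does not support:

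- **That the comparison is biased.** Randomisation balances stage in expectation. A chance imbalance is sampling variation, already reflected in the standard error and the type I error of the test.
- **That stage enters no comparison at all.** The stratifying factor cannot be identified from {16a}, pathology is collected, and baseline characteristics will be tabulated. The text supports only that stage is named in no stratification, model or subgroup.
- **That treatment would affect every nutritional endpoint.** The article gives no figure for any such effect. It can only be said that an effect is possible.

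**Conclusion.** The point holds in limited form. The reasoning in {11d} does not justify setting co-treatment aside, because the endpoints include outcomes that postoperative cancer treatment can affect. The consequence is some lost precision, exposure to chance imbalance and weaker interpretation of both the arms and the data used to size the main study.

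The size is modest. Under the assumptions above, a 15-point imbalance has a chance of about 20–27% with 33 per arm (11–16% with 44). It shifts the comparison by at most about 0.08–0.15 SD, well under one standard error. The power loss is about 1–6 points. Both are smaller if only some stage II–III patients are treated, and the imbalance figures do not apply if the unnamed stratifying factor turns out to be stage. Priority: minor to moderate.

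**What to change.** 1. **Rationale ({11d}).** Keep concomitant care unrestricted, but replace the reason. State that care is left to usual practice in both arms and that postoperative cancer treatment is recorded because it may affect the outcomes.
2. **Recording.** Take postoperative cancer treatment (yes/no, start and stop dates) from the medical record in both arms. Describe it by arm at each visit, together with stage. Do not adjust for treatment received: it follows randomisation and could itself be influenced by the arm.
3. **Analysis.** Confirm that pathological stage is among the pathology data collected. Add it (I versus II–III) as a fixed covariate in the KOQUSS-40 mixed model and the nutritional comparisons, or at least prespecify a stage-adjusted sensitivity analysis. Stage is suitable because the platform cannot plausibly alter it.

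The cost is a few case report form fields filled from existing records and one degree of freedom per model. Patient care does not change.
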